## Abstract

**Background:**

The average life expectancy for people with a severe mental illness (SMI) such as schizophrenia or bipolar disorder is 15 to 20 years less than that for the population as a whole. Diabetes contributes significantly to this inequality, being 2 to 3 times more prevalent in people with SMI. Various risk factors have been implicated, including side effects of antipsychotic medication and unhealthy lifestyles, which often occur in the context of socioeconomic disadvantage and health care inequality. However, little is known about how these factors may interact to influence the risk of developing diabetes and poor diabetic outcomes, or how the organization and provision of health care may contribute.

**Objective:**

This study aims to identify the determinants of diabetes and to explore variation in diabetes outcomes for people with SMI.

**Methods:**

This study will employ a concurrent mixed methods design combining the interrogation of electronic primary care health records from the Clinical Practice Research Datalink (CPRD GOLD) with qualitative interviews with adults with SMI and diabetes, their relatives and friends, and health care staff. The study has been funded for 2 years, from September 2017 to September 2019, and data collection has recently ended.

**Results:**

CPRD and linked health data will be used to explore the association of sociodemographics, illness, and health care–related factors with both the development and outcomes of type 2 diabetes in people with SMI. Experiences of managing the comorbidity and accessing health care will be explored through qualitative interviews using topic guides informed by evidence synthesis and expert consultation. Findings from both datasets will be merged to develop a more comprehensive understanding of diabetes risks, interventions, and outcomes for people with SMI. Findings will be translated into recommendations for interventions and services using co-design workshops.

**Conclusions:**

Improving diabetes outcomes for people with SMI is a high-priority area nationally and globally. Understanding how risk factors combine to generate high prevalence of diabetes and poor diabetic outcomes for this population is a necessary first step in developing health care interventions to improve outcomes for people with diabetes and SMI.

**Trial Registration:**

ClinicalTrials.gov NCT03534921; https://clinicaltrials.gov/ct2/show/NCT03534921

## Introduction

### Background

Severe mental illness (SMI) refers to a set of disabling conditions such as schizophrenia, schizoaffective disorder, or bipolar disorder. People with SMI, who account for around 1% of the population [1], may experience feelings of persecution, hallucinations, problems with mood, impaired cognition, and lack of motivation. These difficulties can have an adverse impact on several areas of life such as housing, employment, relationships, and personal care, which can, in turn, increase the likelihood of mental and physical health problems. They have a reduced life expectancy, living for 15 to 20 years less than the population as a whole, and experience poorer health outcomes [2-5].

Diabetes is a significant contributor to the increased morbidity and mortality experienced by people with SMI. The condition is 2 to 3 times more prevalent in this population [6-8], and complications of diabetes are higher than for people without SMI [9,10]. The link between the metabolic side-effects of antipsychotic medication and diabetes has been well-documented [11-13], but there are additional complexities; other work points to the possibility of a genetic neuroinflammatory mechanism predisposing people toward both conditions [14], which could explain the occurrence of the comorbidity independent of antipsychotic medication [15,16]. Furthermore, other factors have been implicated such as lifestyle health risk factors such as diet [17], smoking [18,19], low levels of physical activity [20], and higher levels of other comorbid conditions [21]. However, little is known about the relative contribution of these factors, or about possible synergistic relationships that may increase the risk of people with SMI developing diabetes or experiencing poorer diabetes outcomes.

There is strong evidence that people with SMI are more likely to be socially disadvantaged than people without SMI [22-24], experiencing reduced access to material, financial, social, or structural resources such as transport, childcare, paid leave, and advocacy services [25]. Accordingly, people with SMI have difficulty navigating health care systems, less capacity to take advantage of health promotion opportunities, and encounter more barriers to taking up interventions designed to prevent or treat illness. Moreover, despite calls for integrated service models that treat the *whole person* [26], such models of service delivery can be thwarted by rigid boundaries between primary and secondary care, unclear practitioner accountability for mental and physical health care [27,28], and diagnostic overshadowing (misattributing physical health problems to mental illness) [29].

There is conflicting evidence about the quality of diabetes care for those with and without SMI [10,30-34]. In addition, little is known about the costs of diabetes screening, monitoring, and management for this group, or about the relationship between diabetes interventions and health outcomes. Furthermore, although a recent study demonstrated that diabetes distress—the emotional burden of managing a serious, chronic condition—is known to significantly affect people with diabetes who do not have SMI [35], there is limited evidence on how diabetes might impact upon the mental health of people who already experience psychological vulnerabilities.

Improving diabetes care for people with SMI is a high priority nationally and globally [36,37]. Understanding how SMI and other risk factors combine to generate high diabetes prevalence and poor diabetes outcomes and how the quality and quantity of health care services and interventions can impact on these risk factors is a necessary first step in developing health care interventions to improve outcomes for people with diabetes and SMI.

### Objectives

This study aims to identify the determinants of diabetes in people with SMI and to explore variation in diabetes outcomes for people with SMI to develop potential health care interventions that can be tested further.

The study has the following objectives:

In people with SMI, to identify which sociodemographic, illness, family history, and lifestyle factors are associated with the development of diabetesIn people with SMI and diabetes, to identify which sociodemographic, illness, family history, and lifestyle factors are associated with variation in diabetes and mental health outcomesIn people with SMI, to compare health care interventions, physical and mental health outcomes in those with diabetes, and those without diabetesIn people with diabetes, to compare health care interventions, physical and mental health outcomes in those with SMI, and those without SMITo understand the factors that influence access to, and receipt of, diabetes care for people with SMI and explore the experience of diabetes health care by people with SMITo compare diabetes care provision for people with and without SMI, and estimate costs for theseTo identify which health care interventions (eg, medication, referrals, and care pathways) may be associated with better diabetes outcomes for people with SMI and diabetes.

## Methods

### Design

The underpinning theoretical framework for the study conceptualizes socioeconomic conditions as a fundamental cause of health inequalities [25]. Under a social inequalities framework, a concurrent triangulation mixed methods design will be used comprising (1) a quantitative longitudinal observational study of anonymized individual patient records of adults diagnosed with SMI in Clinical Practice Research Datalink (CPRD) and (2) a qualitative interview study of people with coexisting SMI and diabetes, their family or friends, and health care staff involved in diabetes and mental health care. Both workstreams will be informed by a synthesis of existing evidence.

The mixed methods design is underpinned by a pragmatic paradigm, which acknowledges that data types, when integrated together, will enable the development of a more complete understanding of health inequalities in this population than would be possible from either method alone [38]. Interrogation of quantitative data from CPRD will be used to generate insights into inequalities through identifying trends, patterns, and correlations, indicating which groups are more at risk of developing diabetes or experiencing poor diabetes outcomes. These data will be complemented by findings from the analysis of qualitative interviews conducted to explore the difficulties people with SMI have in managing their diabetes and accessing services. The quantitative and qualitative data will be integrated iteratively as the study progresses; key findings emerging from the CPRD analysis will be explored further in interviews, and qualitative themes will be used to inform the choice of variables that can be explored in the quantitative dataset (see Figure 1). Key to both the quantitative and qualitative analyses will be exploring the effects of disadvantage and deprivation on risks, outcomes, and experiences for people with SMI and diabetes.

**Figure 1 figure1:**
[figure not shown]
Study Flow Diagram.

### Patient and Public Involvement

The study is supported by DIAMONDS VOICE, a patient and public involvement (PPI) panel that contributes to a wider research program called Diabetes and Mental Illness: Improving Outcomes and Services. The panel was involved in prioritizing the research questions during the design phase of this study and reviewed all patient and public-facing documentation before submission to the National Health Service Research Ethics Committee. The panel will continue to contribute to the study in the following ways: advising on how to ask sensitive questions, acting as practice interviewees, advising on minimizing participant burden, promoting the study at local events, and advising on recruitment and dissemination strategies. Both the project management team and the study steering committee have service user representation to ensure that the patient perspective is incorporated in project decisions.

### Ethical Approval and Data Use Agreement

A data use agreement for CPRD records and linked Hospital Episode Statistics (HES) and Office for National Statistics (ONS) mortality data was granted by the International Scientific Advisory Committee (ref: 17_161R). Approvals for the qualitative study were granted by the National Institute of Health Research Health Research Authority and the Greater Manchester West Research Ethics Committee (ref: 18/NW/0005), following a submission made through the Integrated Research Application System (ref: 235328).

The study is registered on the NIHR Central Portfolio Management System (CPMS; ref: #37024) and ClinicalTrials.gov (record identifier #NCT03534921).

### Quantitative, Longitudinal, and Observational Study

This workstream examines the impact of potential risk factors on the development and the time to onset of diabetes in people with SMI and variation in mental and physical health outcomes in people with comorbid SMI and diabetes. Diabetes health care and outcomes for people with SMI and diabetes will be compared with outcomes for people with either condition alone. Variations in diabetes screening, monitoring, and management will be examined and costs estimated. The role of these interventions in contributing to health outcomes will be explored.

#### Study Population

The primary study population comprises adult patients (age ≥18 years) living in England who are registered with a general practice contributing up to research standard data to CPRD and who have remained within CPRD for the study period, from April 1, 2000, to March 31, 2016.

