#### Data Linkages

Electronically linked data for individuals in the study population will be obtained from the following sources: HES data for hospital admissions [41], ONS for dates and causes of death [42], and the Index of Multiple Deprivation (IMD) for area deprivation at practice and patient level [43].

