#### Health and Health Care Outcomes

The following outcomes listed in Table 2, corresponding to the objectives described above, will be examined.

Analyses may be limited by the quality and availability of data for some of the above variables, but wherever possible, validated code lists will be employed.

**Table 1 table1:** Structure of the Clinical Practice Research Datalink datasets.

Dataset	Population	Specification	Estimated sample size of patients
Dataset A	Adults (≥18 years) with SMI^a^	Longitudinal health care records of adult patients with SMI defined as the presence of a clinical diagnostic code for schizophrenia, affective disorder (divided into bipolar or unspecified affective disorder), and other types of psychoses. Read codes previously tested and applied by the research team [37] will be used to identify the presence of SMI.	33,000
Dataset B (a subset of dataset A)	Adults with a diagnosis of SMI and diabetes mellitus	Diabetes, identified using previously tested and validated Read codes, will be further defined as the presence of a clinical diagnostic code for type 1 diabetes, type 2 diabetes, drug-induced diabetes, or unspecified diabetes. Individuals with a diagnostic code of gestational diabetes, cystic fibrosis, and hemochromatosis will be excluded.	3600 based on a predicted diabetes prevalence of 11.1% [40]
Dataset C (matched controls to dataset B)	Adults with a diagnosis of type 2 diabetes but without SMI	Patients with type 2 diabetes in dataset B will be matched by Clinical Practice Research Datalink to a cohort of patients who have a diagnosis of type 2 diabetes but without SMI (controls) with a case to control ratio of 1:4 on the basis of age, gender, and practice.	14,400

^a^SMI: severe mental illness.

**Table 2 table2:** Health and health care outcomes corresponding to objectives.

Outcome	Objective #
Diabetes status and onset	1
Diabetic and cardiovascular control (measured by recorded hemoglobin A_1c_, blood pressure, and cholesterol levels)	2
Diabetic complications: acute hyperglycemic events, hypoglycemia, microvascular complications (retinopathy, neuropathy, and nephropathy)	2, 4
Diabetic complications: macrovascular complications (coronary artery disease, cerebrovascular disease, and peripheral arterial disease)	2, 3, 4, 7
Hospital admissions for the above conditions	2, 3, 4, 7

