#### Statistical Analysis

It is anticipated that there will be around 5 to 6 years of data on each individual, which will enable more robust analyses than cross-sectional data would permit. Longitudinal data afford better control for unobserved characteristics, at either the individual or practice level that plausibly impact both practice performance and patient outcomes (eg, practice style and culture), and which may otherwise confound important relationships. In addition, repeated observations at practice or patient level allow the investigation of lags in the relationship between diabetes management and outcomes, as the timing of events can be observed. Both these factors are crucial in identifying plausible causal mechanisms linking diabetes management to outcomes.

The potential for confounding will be addressed by matching on index date to avoid inclusion of *ghost* patients, conducting sensitivity analyses, and evaluating the potential for unmeasured confounding and the size of any observed effects.

A range of regression models will be used for statistical analyses, taking account of the hierarchical structure of the data, where, for example, activities are *nested within* patients who in turn are nested within practices. Linear, logistic and survival regressions will be applied as appropriate depending on the outcome variable of interest. Multilevel mixed effects will be estimated to account for the correlation in the longitudinal health records of the same patient, as well as the unobserved correlation at practice level. An outline of planned analyses by study objective is given in Table 3.

Under all objectives, analyses will be conducted in line with the inequalities framework to quantify the absolute and relative effect of social inequalities on quality of care and outcomes. Under objectives 1 and 3, the disparities will be modeled within the SMI population, under objective 2 within the SMI and diabetes population, and both within and between the diabetes populations (SMI and non-SMI) under objectives 4 to 7. Specifically, where sample size permits, analyses will be stratified, for example, by ethnicity and or deprivation and disadvantage markers such as IMD; housing status and rurality will be used as independent variables to estimate gap or gradient effects.

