All statistical models will include a set of relevant patient, local population, and practice covariates where possible to control for confounding and interacting influences potentially masking the relationship between diabetes management and outcomes.

In sensitivity analyses, noncompliance (including refusal of treatment, informed dissent, and nonattendance) will be included as an independent variable in the models. Sensitivity analyses will be conducted with noncompliance treated as either a time-dependent (*expiring*) or time-independent (*nonexpiring*) variable and as specific to the refused treatment or as a general marker of noncompliance. Noncompliance will be used to create *offer of treatment* explanatory variables, facilitating *intention-to-treat* type analyses.

Robustness checks will be carried out to ensure our results are reliable, and plausibility tests to ensure findings are meaningful in practice and can inform policy. Model assumptions will be checked for all analyses, and if they are in doubt, the data will be transformed before analysis or alternative nonparametric analysis methods will be used.

**Table 3 table3:** Summary of statistical analysis plan by study objective.

Objective #^a^	Description	Datasets	Variables	Analysis
1	The impact of key explanatory variables on both diabetes status and time to onset of diabetes	Quantitative dataset A (people with SMI^b^)	Explanatory variables: sociodemographic characteristics, medication use, physical and mental health status, family history of diabetes, biometric data dysregulation, and lifestyle factors	Multilevel modeling: logistic model (diabetes status) and survival model (time to diabetes onset)
2	The impact of key explanatory variables (as above) on diabetes and mental health outcomes	Quantitative dataset B (people with SMI and type 2 diabetes)	Outcomes: diabetic and cardiovascular control; diabetic complications; hospital admissions; mental health outcomes, for example relapses and episodes of depression and anxiety and mortality	Repeated measures mixed models: linear, logistic, and survival models
3	The impact of diabetes status and other explanatory variables (as above) on physical and mental health outcomes	Quantitative dataset A	Outcomes: macrovascular diabetic complications, hospital admissions, mental health outcomes, and mortality	Poisson or negative binomial multilevel models for count outcomes, logistic multilevel models for binary outcomes

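### As written, the eligibility sentence admits only patients who stayed in CPRD for all 16 years, which rules out in-period deaths and contradicts mortality as an outcome

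*Protocol article*

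**What the plan says.** The Study Population section admits adults in England who are registered with a practice contributing research-standard data and "who have remained within CPRD for the study period, from April 1, 2000, to March 31, 2016". The relative clause describes the patients, not the practices. No exception is given for people who died, transferred out or registered later.

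Four other places bear on this:

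- **Data Linkages:** the linked sources for individuals in the study population include "ONS for dates and causes of death".
- **Table 2 (Health and Health Care Outcomes):** mortality is an outcome for objectives 2, 3, 4 and 7.
- **Table 3 (Statistical Analysis):** the objective 2 row ends with "episodes of depression and anxiety and mortality". The objective 3 row reads "Outcomes: macrovascular diabetic complications, hospital admissions, mental health outcomes, and mortality", and the objective 4 row carries the same outcomes forward.
- **Statistical Analysis, opening paragraph:** "It is anticipated that there will be around 5 to 6 years of data on each individual".

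**The concern.** An eligibility rule should use only what is known at entry. This one requires presence on the last day of follow-up, so it selects on the future. Anyone who died, moved practice or joined after the start date is ineligible.

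Mortality is the outcome hit directly, because it cannot be observed inside the window. The other analyses would be affected through selection: time to diabetes onset, complications, admissions and the deprivation gradients would be estimated only in people who lived and stayed put for 16 years. The Background describes this population as living 15 to 20 years less than the general population and as socially disadvantaged, so those removed are unlikely to resemble those kept. Dataset B is a subset of dataset A and inherits the rule. If the rule also governs the matched controls in dataset C, the comparison of people with and without SMI is exposed wherever survival or retention differs between the groups. Adjusting for covariates does not bring back deaths that were left out at extraction.

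**Working it through.** **Inputs from the document.** Window: 1 April 2000 to 31 March 2016 (Study Population). Data per person: 5 to 6 years (Statistical Analysis). Dataset sizes: 33,000, 3,600 and 14,400, with 11.1% prevalence and 1:4 matching (Table 1).

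**Table 1 sizes.** 33,000 × 0.111 = 3,663, against 3,600 stated (within 2%). 3,600 × 4 = 14,400, exact. Table 1 is consistent with itself, but it does not show how the 33,000 was obtained and so does not bear on the rule.

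**Length of the window.** Counting both end dates there are 5,844 days; 5,844 / 365.25 = 16.0 years.

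**Mortality.** Eligible means present to 31 March 2016. Dying before that date means not present to it. No eligible patient can therefore have died earlier in the study period, and the expected number of in-period deaths is 0. This needs no assumption about death rates.

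**Years of data.** Under the rule everyone has 16 years in the database, which is 33,000 × 16 = 528,000 person-years. At 5 to 6 years each the total is 33,000 × 5 = 165,000 to 33,000 × 6 = 198,000. The stated figure does not follow from the rule.

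The reverse check is an upper bound. Let p be the share present for all 16 years and m the mean time in CPRD within the window. Each such person contributes 16 years and nobody contributes less than 0, so 16p ≤ m and p ≤ m/16:

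| m (years) | Largest possible p | Out of 33,000 |
|---|---|---|
| 5 | 5/16 = 31% | 10,312 |
| 6 | 6/16 = 38% | 12,375 |

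The rule requires p = 100%. The bound holds whatever the distribution of follow-up, provided that 5 to 6 years is a mean of time in CPRD within the window.

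**Illustration of the deaths at stake.** The document gives no death rate, so 1% to 3% per year is an assumption. In a closed cohort followed for 16 years, the share dying is 1 − exp(−16 × 0.01) = 15% to 1 − exp(−16 × 0.03) = 38%. In an open cohort of 33,000 followed for 5.5 years each, deaths would be 33,000 × (1 − exp(−5.5 × 0.01)) ≈ 1,770 to 33,000 × (1 − exp(−5.5 × 0.03)) ≈ 5,020. The finding does not rest on these figures.

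**The case against.** The strongest answer is that the sentence is loosely worded and means only that patients contributed data at some time within the window. The rest of the article supports that intent: linked death dates, mortality outcomes, survival models, matching on index date and about 5 to 6 years of data each all presuppose staggered entry and exit. The article is also condensed, and it cites a separately approved data application that is not shown. Entry, exit and censoring dates may stand there, and their absence here is no fault.

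Most of this stands as evidence of intent, but it does not rescue the sentence. The article states a positive rule with calendar dates, and anyone who built the cohort from it would get a different population from the one the outcomes need.

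On follow-up the objection has more force. The 5 to 6 years might count only data after an SMI or diabetes diagnosis, which could be shorter than registration. The article does not say so, but this is the weaker of the two conflicts. That reading would leave the conflict over mortality untouched.

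Three stronger readings are tempting and should be resisted:

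- A reader might infer that the extract was in fact restricted and that the results will be biased. The article does not show this.
- A reader might turn 5 to 6 years into an exit rate and a retention percentage. With everyone present at the start and a constant exit rate h, solving (1 − exp(−16h))/h = 5 to 6 gives about 5% to 9% retained. But the stated figure may also reflect late registration and late diagnosis, so it does not identify an exit rate.
- A reader might infer that 33,000 patients could not be found under the rule. The article gives no count of people with SMI, ever or continuously registered, so this cannot be shown.

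**Conclusion.** The eligibility sentence is wrong as written and should be corrected. Its conflict with mortality as an outcome for four objectives, and with the death linkage, follows from the text alone: in-period deaths are zero under the rule. Its conflict with the expected length of data is conditional: if 5 to 6 years is mean time in CPRD within the window, at most 31% to 38% of people could satisfy a rule that everyone must satisfy.

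Survivor and retention bias in the onset, complication, admission and deprivation analyses would follow only if the sentence was applied literally. Neither the direction nor the size of that bias can be worked out from the document. The illustrative death counts depend on an assumed 1% to 3% annual rate.

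**What to change.** Reword the Study Population section as an open cohort: adults registered with an up-to-standard practice at any time between 1 April 2000 and 31 March 2016, entering when they first meet all criteria, and followed until the earliest of death, leaving the practice, the practice's last data collection or 31 March 2016. State that no eligibility condition uses data after entry, and say whether the same rule governs dataset C. Add a few words on what the 5 to 6 years counts.

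Then check the extraction specification against the new sentence. If the extract was already open, the cost is that one correction. If it was restricted as written, it must be redrawn with its linkages before any mortality or time-to-event analysis; the document does not allow that cost to be estimated. In either case follow-up differs between people, so the models must allow for it (censoring in survival models, person-time in count models). That detail can sit in the full analysis plan.
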